Moreover, the Strength and Difficulties Questionnaire (SDQ) is a 25-item parent-rating screening tool used to screen a child’s behavioural and emotional problems [62]. SDQ comprises five subscales: conduct problems (e.g., fighting with others, well-behaved), hyperactivity (e.g., restlessness, easily distracted), emotional symptoms (e.g., frequent worries, often unhappy), peer problems (e.g., being picked on or bullied, liked by other children), and prosocial behaviour (e.g., being considerate of others, shares with other children) [62]. Each subscale contains five items. Each item is rated on a 3-point response scale: 0 = not true, 1 = somewhat true, and 2 = certainly true. The scores from each domain will be summed, and a ‘total difficulties score’ will be calculated by summing the four deficit-focused subscales (excluding prosocial behaviour). Z-scores will be calculated for each domain, with higher Z-scores indicating fewer difficulties. The cut-off scores for ‘borderline’ and ‘abnormal’ classifications correspond to the 80th and 90th percentiles (20th and 10th for prosocial behaviour scale), respectively. Specifically, scores falling within the bottom 10% of the normative distribution indicate potential problems of clinical significance. The Malay version of parent-rated SDQ is readily available and has shown acceptable internal consistency, with Cronbach’s alpha values above 0.70 for all subscales, except for conduct and peer problems [63].

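### The SDQ scoring text gives conflicting directions: the Z-score and bottom-10% sentences fit the percentile cut-offs only if the deficit Z-scores are reversed, which is not written

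*Protocol article*

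**What the plan says.** All the relevant text is in the SDQ paragraph of the protocol article, under Parent report questionnaires. It makes four statements in sequence.

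1. **Raw scoring.** "Each item is rated on a 3-point response scale: 0 = not true, 1 = somewhat true, and 2 = certainly true". Each subscale has five items. The four deficit-focused subscales are summed, without prosocial behaviour, into a total difficulties score.
2. **Z-score direction.** "Z-scores will be calculated for each domain, with higher Z-scores indicating fewer difficulties". No sign change is mentioned.
3. **Cut-offs.** The borderline and abnormal classes "correspond to the 80th and 90th percentiles (20th and 10th for prosocial behaviour scale), respectively".
4. **Clinical significance.** In a sentence that opens with 'Specifically', and so reads as an elaboration of statement 3: "scores falling within the bottom 10% of the normative distribution indicate potential problems of clinical significance". Neither the scale (raw or Z) nor the domain is named.

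Elsewhere, the Objectives section treats behavioural profile as an additional independent variable. The Statistical analysis plan section lists emotional and eating behaviour among the group comparisons and the ASD-group models. The Sample size section names beta diversity and nutritional status as the primary outcomes.

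**The concern.** Direction changes within one paragraph and the reader is not told. Statements 1 and 3 put the problem tail of the deficit scales at the top. Statements 2 and 4 put it at the bottom, and statement 4 is presented as a restatement of statement 3. Standardising a score does not change its direction, so statement 2 is not true of an ordinary Z-score of a deficit sum.

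Two errors could follow if the text is carried into a scoring script as it stands:

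- The bottom-10% rule could be run on raw deficit scores, which selects the children with the fewest problems.
- Ordinary, unreversed Z-scores could be computed and then interpreted with the stated direction. Any association with the microbiota, GI symptoms or severity would then be described with the wrong sign for the four deficit domains and the total.

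This differs from a detail left out for brevity. The article states item reversals for the CEBQ, the AQ and the CSHQ. For the SDQ it states a direction that its own raw scoring does not produce.

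**Working it through.** **Inputs from the article.** Items are scored 0 to 2 with five items per subscale, so a raw subscale runs from 0 to 5 × 2 = 10 and total difficulties from 0 to 4 × 10 = 40. The abnormal cut-off is the 90th percentile (10th for prosocial). The competing rule is the bottom 10%. No sample size or power figure depends on this point, so there is no plan figure to reproduce.

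**Step 1: test each statement on each possible scale.**

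| Scale | Higher Z = fewer difficulties (2) | Abnormal at 90th percentile (3) | Bottom 10% = clinical group (4) |
|---|---|---|---|
| Raw deficit score | not applicable | right tail | wrong tail |
| Ordinary Z of deficit score | false | right tail | wrong tail |
| Reversed Z of deficit score | true | wrong tail | right tail |
| Prosocial, raw or ordinary Z | true for Z | 10th percentile applies: right tail | right tail |

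For the deficit scales no single row makes statements 3 and 4 both right. They agree only if statement 3 is read on raw scores and statements 2 and 4 on reversed Z-scores. The prosocial exception in statement 3 shows that it is written for raw scores: if every domain already ran from worse to better, prosocial would need no separate cut-off. For prosocial itself nothing conflicts.

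**Step 2: distance between the two rules on one scale.** The 90th percentile is z = +1.282 and the 10th is z = −1.282, in opposite tails.

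**Step 3: discrete scores.** The article gives no norms, so beta-binomial norms were assumed, with mean 15%, 25% or 40% of the maximum and beta parameters 6p and 6(1 − p).

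| Scale | Mean, % of maximum | 90th percentile | 10th percentile | Share of norm group at or below 10th |
|---|---|---|---|---|
| Subscale 0–10 | 15 | 4 | 0 | 37.4% |
| Subscale 0–10 | 25 | 5 | 0 | 18.2% |
| Subscale 0–10 | 40 | 7 | 1 | 15.9% |
| Total 0–40 | 15 | 14 | 0 | 14.0% |
| Total 0–40 | 25 | 20 | 2 | 13.7% |
| Total 0–40 | 40 | 27 | 6 | 12.3% |

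On raw scores the two rules share no flagged score in any of the six cases. With the sign reversed, the lower tail cut at the Z-value of the raw 90th percentile flags exactly the same scores as the raw 90th-percentile rule, in all six.

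**Step 4: conditional size of a misreading.** Assume normal scores and an ASD mean shifted by d SD above the norm on a deficit scale. The article gives no value for d. The share flagged is P(Z > 1.2816 − d) under the 90th-percentile rule and P(Z < −1.2816 − d) under a raw bottom-10% rule.

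- d = 0.5: P(Z > 0.7816) = 21.7%; P(Z < −1.7816) = 3.7%
- d = 1.0: P(Z > 0.2816) = 38.9%; P(Z < −2.2816) = 1.1%
- d = 1.5: P(Z > −0.2184) = 58.6%; P(Z < −2.7816) = 0.3%

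At d = 1.0 in 40 ASD children this is 0.389 × 40 ≈ 16 against 0.011 × 40 ≈ 0.4.

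**Step 5: sign of associations.** For any variable M, corr(−Z, M) = −corr(Z, M). The size is unchanged. Only the direction is misread, and only if Z is left unreversed but interpreted as statement 2 describes.

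**The case against.** The strongest defence is that the paragraph can be read consistently. The Z-score sentence declares a direction that can hold for a deficit domain only if the score has been reversed. On that scale the bottom 10% are the most affected children, the same group as the raw 90th-percentile cut-off. The only sentence that defines the borderline and abnormal classes also uses the correct tails, while the bottom-10% sentence is interpretive and defines no class. Scoring steps are often left to the instrument's guide or the analysis plan. The article gives no SDQ item-reversal key either, and that is ordinary condensation.

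Much of this stands. A reader might infer that the plan would flag the least affected children as abnormal, or that every behavioural association would change sign. The documents support neither. The first needs an analyst to read the bottom-10% sentence as a raw-score rule and to set aside the explicit cut-offs and the stated Z direction. The second fails because prosocial is unaffected, a tail cut-off does not alter the sign for a continuous score, and a reversed Z with a declared direction remains interpretable. The Statistical analysis plan section does not name the SDQ or say whether its class, raw score or Z-score enters a model.

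What the defence does not remove is that the consistent reading depends on a reversal the text does not contain and on a silent change of scale between two sentences joined by 'Specifically'. That is conflicting wording on the page, not merely an omitted detail.

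**Conclusion.** The point holds as an unreconciled scale and sign convention in the SDQ paragraph. The percentile cut-offs are right for raw scores. The Z-direction sentence is untrue of ordinary Z-scores for four of the five domains and for a Z-score of the total, if one is formed. The bottom-10% sentence fits only prosocial or reversed Z-scores. Misclassification or a misread direction is possible but conditional on how an analyst resolves the text, and it is not the likeliest outcome.

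The percentages (38.9% against 1.1% at a 1 SD shift; 21.7% against 3.7% and 58.6% against 0.3% at 0.5 and 1.5 SD) only illustrate what a raw-score reading would do. They rest on assumed normality and assumed shifts. The SDQ is an additional independent variable, so the primary outcomes and the sample size are unaffected. The wording should be corrected before analysis.

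**What to change.** In the SDQ paragraph, or in the analysis plan if that governs scoring:

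- Keep the article's own percentile cut-offs as the classification rule and say that they apply to raw scores: 80th and 90th for total difficulties and the four deficit subscales, 20th and 10th for prosocial only.
- Either state that the deficit-domain Z-scores (and that of the total, if one is formed) are multiplied by −1, or delete the clause saying that higher Z-scores mean fewer difficulties.
- Restrict the bottom-10% sentence to the prosocial scale or to the reversed Z-scores.
- Check that the scoring code follows the chosen convention.

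The cost is one or two sentences and a code check, with no new data. Results are expected in December 2026, so this can be settled before the analysis.

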### Reimbursement

Participants are reimbursed a book voucher (RM50) as appreciation for their participation upon receipt of the stool sample and the parents’ questionnaire.

### Statistical analysis plan

Data analysis will be conducted using R software and its available packages. The differences in microbiota profiles, socio-demographic factors, emotional and eating behaviour, and nutritional status between children with ASD and TD children will be compared using the chi-square/Fisher’s exact test and ANOVA where appropriate. Student’s t-test will be applied to compare BMI and age between groups. Pre-filtering and inference of correlations will be performed using the Sparse Correlations for Compositional Data (SparCC) correlation metric [66], with a minimum R-value threshold of 0.35. SparCC will be used to correlate salivary and faecal bacterial markers detected in saliva and faecal samples from the same child. The associations between microbiota profiles, socio-demographic factors, emotional and eating behaviour, autism severity, sleep quality, gastrointestinal symptoms, and nutritional status among children with ASD will be modelled using mixed-effects logistic regression (MELR) model and random forest. Normality, linearity, homoscedasticity, and multi-collinearity will be assessed to ensure that the assumptions of regression models are met. Potential confounders, including age, and socioeconomic status will be adjusted for fixed effects. Model assumptions will be performed using DHARMa package in R to assess dispersion, zero-inflation and overall fit [67]. In case of heteroscedasticity or overdispersion, corrective strategies will include the use of an observation-level random effect, modelling dispersion or zero-inflation with glmmTMB [68], or applying bias-reduced logistic regression (Firth correction) [69] or bootstrap inference to mitigate small-sample bias [70]. Study results are expected in December 2026.

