**Methods and analysis:**

This observational, age-matched, case-control study is conducted in Malaysia among 40 male children with ASD and age-matched with 40 TD healthy controls aged 4–10 years. The dependent variables include the microbiota profile, identified through metagenomic sequencing analysis of saliva and faecal samples, and autism severity, assessed through validated questionnaires. Independent variables include nutritional status, determined through Subjective Global Nutrition Assessment (SGNA), anthropometry and dietary measurements, gastrointestinal symptoms, eating behaviour, behavioural profile, and sleep quality. Data collection is expected to be completed by June 2026. The study nature may limit causality establishment. Analyses will use chi-square/ANOVA for group comparisons, SparCC for microbiota correlations, and mixed-effects logistic regression to model associations.

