### Sample size

This study aims to compare the microbial community structure between the ASD and TD healthy groups and within the groups, generating plausible distances relevant to the study objectives. Beta diversity is used to estimate the sample size or statistical power for this study. The recommended sample size is 60 participants, determined based on calculations using data from a study conducted by Li et al. [31]. Due to the limited availability of similar studies, this prior research served as a reference to obtain appropriate variance estimates [31]. The total study sample size of 60 participants has been adjusted to account for a possible 30% dropout rate; thus, this study aims to recruit 80 participants (40 children with ASD and 40 TD healthy children). The primary outcomes are microbial beta diversity and nutritional status. Secondary microbiota comparisons will be adjusted for multiple testing using the Benjamini-Hochberg false discovery rate, and post-hoc power analyses will be conducted to assess adequacy for multivariate models.

The study included only male children to eliminate potential gender bias, as the male predominance in ASD has been well-documented in epidemiological studies and widely recognised in the field [32–34]. This approach also ensures greater homogeneity in the demographic and microbiome datasets, thereby enhancing the precision and reliability of the findings.

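### The tests named for ASD-TD differences in microbiota profiles do not fit beta diversity, the primary outcome on which the study is sized

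*Protocol article*

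**What the plan says.** The Sample size section of the protocol article states: "The primary outcomes are microbial beta diversity and nutritional status". It also states: "Beta diversity is used to estimate the sample size or statistical power for this study". It describes the comparison as one that will "compare the microbial community structure between the ASD and TD healthy groups and within the groups, generating plausible distances" relevant to the objectives.

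The Statistical analysis plan section assigns tests for "The differences in microbiota profiles, socio-demographic factors, emotional and eating behaviour, and nutritional status between children with ASD and TD children". These are chi-square or Fisher's exact test and ANOVA, to be used where appropriate. The abstract shortens this to "Analyses will use chi-square/ANOVA for group comparisons".

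The same section gives every other named method a different job:
- the t-test is for BMI and age;
- SparCC relates saliva to stool markers within a child;
- mixed-effects logistic regression and random forest model associations among children with ASD, so they do not compare ASD with TD.

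The sequencing methods define one diversity index, Shannon, which is an alpha index. No beta-diversity distance is named.

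**The concern.** Beta diversity is one value per pair of children, not one value per child. Chi-square, Fisher's test and ANOVA all assume independent observations, and a set of pairwise distances is not independent. The quantity that sized the study therefore has no matching test among those named for the ASD-TD comparison.

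Two outcomes are possible. ANOVA may be run on per-child summaries, and then a primary outcome is untested or only partly tested. Or it may be run on the distances, and then the p-value does not have its nominal meaning. In either case the distance and the test could still be chosen after the data are seen.

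**Working it through.** **The plan's own figure.** "The recommended sample size is 60 participants", "adjusted to account for a possible 30% dropout rate", with the aim to "recruit 80 participants (40 children with ASD and 40 TD healthy children". The 60 cannot be reproduced, because the article gives no alpha, power, effect size, distance variance or test. On the dropout step, 60 × 1.3 = 78, close to 80, whereas 60/(1 − 0.30) = 85.7, or 86. With 30% loss, 80 leaves 80 × 0.70 = 56, or 28 per group. This is a side point, but it sets the group sizes examined below: 28, 30 and 40.

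**Dependence at 40 + 40.**
- All distances: 80 × 79/2 = 3,160.
- Within ASD: 40 × 39/2 = 780. Within TD: 780. Between groups: 40 × 40 = 1,600. Sum: 3,160.
- Each child enters 39 + 40 = 79 of them. ANOVA would treat 3,160 values from 80 children as independent.

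**Size of the error with no true group difference.** The documents give no community model and no distance, so the following are assumptions. The distance is Bray-Curtis, and three models were used:
- Dirichlet, 50 taxa, total concentration 10;
- log-normal, 100 taxa, between-child SD 1.5 on the log scale;
- zero-inflated log-normal, 200 taxa, SD 2, half the entries zero.

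There were 1,000 replicates per cell (Monte Carlo SE at most √(0.25/1000) = 1.6 points). PERMANOVA used 199 permutations and 300 replicates (SE about √(0.05 × 0.95/300) = 1.3 points) and was not run at 28 per group. Entries are rejection rates at nominal 5%, as the range over the three models.

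| Analysis | 28 per group | 30 per group | 40 per group |
|---|---|---|---|
| ANOVA, three classes (within ASD, within TD, between) | 32-53% | 34-51% | 41-58% |
| ANOVA, within ASD vs within TD | 39-59% | 40-57% | 47-65% |
| ANOVA, each child's mean distance to own group | 30-34% | 30-31% | 32% |
| ANOVA, pooled within vs between | 1.5-3.8% | 1.5-3.3% | 1.5-4.1% |
| ANOVA, first ordination axis | 4.8-5.5% | 4.5-6.2% | 3.2-6.0% |
| PERMANOVA | not run | 4.7-5.7% | 3.3-5.7% |

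The error depends on the contrast. Comparing the two within-group sets, alone or as part of three classes, inflates it six-fold or more. Pooling within against between makes the test conservative. The ordination axis holds about 5% but tests one axis, not the whole distance structure. PERMANOVA uses the whole matrix and holds its level.

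**The case against.** A reader might infer that the plan has fixed an invalid test that would find a false ASD-TD difference about half the time. The document does not support that reading, for four reasons:
- It never says that ANOVA will be run on pairwise distances. Distances appear only in the sample-size paragraph.
- The tests are qualified by the words where appropriate. One sentence covers microbiota, socio-demographic, behavioural and nutritional variables together, and ANOVA is a reasonable choice for a Shannon index or a single abundance.
- The error rate rests on an assumed community model and distance, and it changes direction with the contrast. Pooled within versus between, itself a direct reading of the sample-size wording, rejects too seldom.
- Untested or badly inflated are not the only possibilities. ANOVA on an ordination axis has about the right level, although it covers only part of the outcome.

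All of this stands, and it limits the claim.

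It can also be said that an article may leave the beta-diversity test to a fuller plan. That argument is weaker here. The article does name the tests for ASD-TD differences in microbiota profiles, and the same section goes into detail elsewhere (a SparCC threshold, model diagnostics, Firth correction). The qualifier only selects among chi-square, Fisher and ANOVA, and none of the three is a test of a distance matrix. So the stated method fits its primary outcome poorly. PERMANOVA is one valid replacement among several.

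**Conclusion.** The point holds in this form: the tests named for ASD-TD microbiota differences do not validly test beta diversity, although it is a primary outcome and the stated basis of the sample size. This follows from the text alone and needs no simulation.

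The size of the consequence is conditional. If ANOVA stays with per-child values, the loss is an untested or partly tested primary outcome. If it is applied to distances, the false-positive rate is roughly 30-65% for three-class or within-ASD versus within-TD contrasts, and about 1-4% for pooled within versus between. Those ranges assume Bray-Curtis distance, the three community models above and 28 to 40 children per group; other models would move them. The article expects data collection to end in June 2026 and results in December 2026. The wording should be settled before the analysis begins.

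**What to change.** In the Statistical analysis plan section, and in the matching sentence of the abstract:
- Name a permutation test on the distance matrix, for example PERMANOVA, as the ASD-TD test of community structure, with one pre-specified distance (such as Bray-Curtis or Aitchison), separately for stool and saliva.
- Make ASD/TD the tested factor, with age and socioeconomic status, the confounders the section already names, as terms. Permute children, not distances. If matched pairs are kept in the analysis, make the permutations respect the age matching.
- Add a dispersion check (PERMDISP), so that a difference in spread is not reported as a shift in composition.
- Keep ANOVA for per-child scalars such as the Shannon index.

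The cost is a few sentences of wording and a little more analysis work with standard R functions. No new data, samples or children are needed.

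### The stated ASD-versus-TD tests (chi-square/Fisher's exact, ANOVA) do not test a distance matrix, so they do not match beta diversity, the primary outcome on which the study is sized

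*Protocol article*

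**What the plan says.** **Outcome and sizing (Sample size section).** "The primary outcomes are microbial beta diversity and nutritional status". The same section says: "Beta diversity is used to estimate the sample size or statistical power for this study". It gives the aim as to "compare the microbial community structure between the ASD and TD healthy groups and within the groups, generating plausible distances relevant to the study objectives", and then: "The recommended sample size is 60 participants", raised to 80 (40 per group) for dropout.

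**Group comparison (Statistical analysis plan section).** It states that "differences in microbiota profiles, socio-demographic factors, emotional and eating behaviour, and nutritional status between children with ASD and TD children will be compared using" a choice of tests: chi-square or Fisher's "exact test and ANOVA where appropriate". Student's t-test is reserved for BMI and age. The abstract condenses this to: "Analyses will use chi-square/ANOVA for group comparisons, SparCC for microbiota correlations, and mixed-effects logistic regression to model associations".

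**Other methods in the same section.** SparCC correlates saliva and stool markers from the same child. Associations "among children with ASD will be modelled using mixed-effects logistic regression (MELR) model and random forest". Firth correction and the bootstrap are fallbacks for the regression models.

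**Multiplicity (Sample size section).** Benjamini-Hochberg control is already stated for the secondary microbiota comparisons.

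**The concern.** Beta diversity is a property of pairs of children. The data are a symmetric matrix of distances in which every child appears once against each of the others. A test of whether the two groups differ has to work on that matrix as a whole, with the child as the unit. Chi-square and Fisher's exact test need counts of independent children. ANOVA needs independent observations, one or more per child, with a known error structure. Neither takes a distance matrix as its input.

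The list of group tests therefore serves the other primary outcome, nutritional status, but contains nothing that fits the one used to size the study. Whoever runs the analysis must either depart from the stated tests or force the distances into one of them. In the second case the error rate depends on which sets of distances are contrasted, and the article does not fix that. The contrast could be chosen after the data are seen.

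**Working it through.** **1. Can the plan's own figure be reproduced?** No. The article attributes the 60 to variance estimates from one earlier study. It gives no distance, effect size, significance level, power or test, so the calculation cannot be traced to any test.

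**2. Does any named method test ASD against TD on beta diversity?**

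| Method named | Stated use | Tests a between-child distance matrix, ASD vs TD? |
|---|---|---|
| Chi-square/Fisher's exact | Group differences | No: categorical counts |
| ANOVA | Group differences | No: independent scalar values |
| Student's t-test | BMI and age | No |
| SparCC | Saliva–stool correlation within a child | No |
| Mixed-effects logistic regression, random forest | Associations within the ASD group | No: no TD comparison |
| Firth correction, bootstrap | Fallbacks for the regressions | No |

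The section on sample collection and analysis lists the Shannon index and relative abundances for each participant. Neither is a beta-diversity measure.

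**3. How many distances, and how dependent?** With N children there are N(N−1)/2 distances, and each child enters N−1 of them.
- N = 60: 60 × 59/2 = 1,770. With an assumed 30 per group, 2 × (30 × 29/2) = 870 are within groups and 30 × 30 = 900 between. Each child enters 59.
- N = 80: 80 × 79/2 = 3,160. With 40 per group, 2 × (40 × 39/2) = 1,560 are within groups and 40 × 40 = 1,600 between. Each child enters 79.

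**4. What would happen if ANOVA were run on those distances?** This is a conditional check, with assumptions that are not in the article. Both groups were drawn from the same Dirichlet community, so the null is true. Bray-Curtis distances were used, with a two-sided nominal 5% level, 1,000 runs per scenario and 199 permutations for PERMANOVA. The Monte Carlo standard error at 5% is √(0.05 × 0.95/1000) ≈ 0.7 points. A two-group ANOVA is the same as the equal-variance t-test. Rejection rates:

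| Per group | Taxa | Concentration | Within-ASD vs within-TD | Three groups (two within, one between) | Within vs between | PERMANOVA | ANOVA on first ordination axis |
|---|---|---|---|---|---|---|---|
| 30 | 50 | 5 | 53.9% | 47.8% | 1.4% | 3.9% | 3.9% |
| 30 | 50 | 20 | 57.4% | 49.8% | 1.4% | 4.8% | 3.7% |
| 30 | 200 | 20 | 53.4% | 46.0% | 2.0% | 5.1% | 5.0% |
| 40 | 50 | 5 | 55.7% | 47.6% | 2.6% | 4.4% | 5.4% |
| 40 | 50 | 20 | 62.0% | 56.8% | 1.2% | 4.4% | 4.5% |
| 40 | 200 | 20 | 59.3% | 52.8% | 2.5% | 5.1% | 4.6% |

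A separate simulation (80 taxa, 600 runs, 28 to 40 per group) agrees: 56–61%, 49–57% and 1–3% for the three distance contrasts, and 5.0% for PERMANOVA at 30 per group.

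**5. Reading.** On raw distances, ANOVA rejects about ten times too often for two contrasts and too seldom for the third. PERMANOVA and an ANOVA on one axis score per child both stay near 5%. The axis score, however, covers only one dimension of the community difference.

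**The case against.** A reader might infer that the plan will run ANOVA on the pairwise distances and that the primary p-value is therefore uninterpretable. The article does not support that. It never says which microbiota quantity goes into ANOVA, its wording allows judgement about when each test applies, and the outputs it lists per participant are one value per child. The mention of distances stands in the sample-size rationale, not in the analysis section. The highest rejection rates also belong to a contrast of spread (within-ASD against within-TD). The contrast nearest to the real question, within against between, errs in the conservative direction. All of this stands, and it makes the error rates conditional.

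It can also be said that a journal article condenses, and that the distance and test may be in a fuller plan. That would answer a silence, but here the article states a family of tests for the microbiota comparison, in the analysis section and again in the abstract, and no member of it fits a distance matrix. Latitude in choosing among the listed tests does not help when none is suitable.

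A second stronger reading is that sending relative abundances to ANOVA is itself an error, since SparCC shows that compositionality was recognised. The sentence does not mention relative abundances, no error rate was computed for that case, and log-ratio models are one option among several. It remains a suggestion only.

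**Conclusion.** The mismatch holds on the text alone and needs no simulation: beta diversity is a primary outcome and the sizing basis, and no stated ASD-versus-TD test addresses it. The sizes are conditional. If ANOVA were applied to raw pairwise distances, null rejection at nominal 5% would be roughly 46–62% or 1–3%, depending on the contrast. These figures rest on simulated Dirichlet communities, Bray-Curtis distance and equal groups of 28 to 40, and other communities would shift them. If ANOVA were applied to one scalar per child, the error rate would be sound, but overall beta diversity would go untested. Nothing here shows whether 60 children give enough power for a distance-based test, because the basis of the 60 is not given.

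**What to change.** - In the Statistical analysis plan section, and in the matching sentence of the abstract, replace chi-square/ANOVA for the beta-diversity comparison with PERMANOVA on one distance and one taxon table, both named in advance. The taxon table needs naming because the article mentions several profiling tools (CCMetagen, One Codex, Kraken2 with Bracken, MetaPhlAn4).
- Account for the age matching: include age as a term, or permute within matched pairs if the pairs are kept in the analysis.
- Add a dispersion check (PERMDISP), because PERMANOVA can also respond to a difference in spread.
- Keep ANOVA and t-tests for outcomes with one value per child, such as the Shannon index. Keep the Benjamini-Hochberg control already stated for secondary microbiota comparisons.
- Optionally, use a log-ratio method for individual taxa.

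The cost is wording. R is already the stated software and standard packages run these tests. No change to recruitment, sampling or sequencing is needed. The change is best made before the group comparison is run; the article expects data collection to finish in June 2026 and results in December 2026. If a fuller plan already names a suitable test, the article's wording should be brought into line with it.
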